#### Evaluation of wellbeing, perceived burden, and (job) satisfaction outcomes in informal caregivers, and health and social care practitioners

Table 4 summarises the effectiveness outcome measures used for informal caregivers and health and social care practitioners. Regarding indicators of wellbeing, perceived burden, and (job) satisfaction, we hypothesise more favourable results at follow-up compared to baseline measurement. Selected methods and instruments aim to provide a complete and comprehensive overview of perceived wellbeing, burden and satisfaction of participants engaged in the implementation of the ValueCare approach.

**Table 4 Tab4:** Effectiveness outcomes in informal caregivers and health and social care practitioners

Outcome	Outcome measure(s)	Methods and instruments	Target group(s)
Wellbeing	Physical HR-QoL Mental HR-QoL	PROMIS-10 [43]	All
Perceived burden	Carer burden	iMTA Valuation of Informal Care Questionnaire (iVICQ) [54]	Informal caregivers
		Zarit Burden Interview 4-item [42, 55]	
	Autonomy and control	Adult Social Care Outcomes Toolkit [42, 56]	
Job satisfaction	Working conditions	Culture of Care Barometer tool [57]	Health and social care practitioners
	Satisfaction	Minnesota Satisfaction Questionnaire—Short Form [58]	
	Work-related burnout	Copenhagen Burnout Inventory [59]	

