### Objectives

The aim of the study is to evaluate the ValueCare approach, using a pre-post controlled design, measuring the benefits for each one of the target groups (older people using health and social care services, their informal caregivers, and health and social care practitioners), and thus to be able to properly evaluate implementation outcomes. The specific objectives are:To compare the benefits of the ValueCare approach versus usual care for older people with regard to indicators of health, wellbeing, quality of life, lifestyle behaviour, and health and social care use.To evaluate the benefits of the ValueCare approach for older people’s caregivers (e.g. relatives, friends), and health and social care practitioners in terms of wellbeing, perceived burden and (job) satisfaction.To evaluate the acceptability, appropriateness, feasibility, fidelity, and costs of the ValueCare approach.

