### Hypotheses

Our hypothesis is that older people in the intervention group (i.e. individuals benefiting from ValueCare) have more favourable results with regard to indicators of health, wellbeing, quality of life, lifestyle behaviour, and reduced health and social care usage compared with older people participating in the control group (i.e. individuals receiving ‘usual care’). With respect to informal caregivers and health and social care practitioners, we expect a lower caregiver burden, and improved wellbeing and (job) satisfaction among participants in the intervention group. Furthermore, we hypothesise the costs of care for the intervention group will be lower, compared to the control group.

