## Methods/design

### Study design

The evaluation of ValueCare has a pre-post controlled design with an intervention group (using the ‘ValueCare approach’) and a control group (‘care as usual’). Measurements are taken at baseline (*T*_0_), after 12 months (*T*_1_; the end of the ‘ValueCare approach’ intervention period), and at 18 months (*T*_2_) [32, 34, 35]. In each of the seven European countries, intervention and control sites (GP practices, community centres for health and wellbeing, and hospitals) are chosen. Table 1 shows the timeline of enrolment, interventions and assessments for this study. Baseline data collection is scheduled to commence by the end of 2021.

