### Participants

The ValueCare target group consists of older people living with: (1) medical conditions and/or disabilities, (2) frailty and/or, (3) mild to moderate cognitive impairment; also their informal caregivers (e.g. relatives, friends), and health and social care practitioners will be involved in the study. Each site in the seven participating countries performs the study in accordance with the contextual and organisational factors and capacity (see Table 2).

**Table 2 Tab2:** Target group per site

Site	Target group of older people
Athens (Greece)	Type II Diabetes Mellitus and hypertension as comorbidity, living independently in the community
Coimbra (Portugal)	Patients/clients with no or mild cognitive impairment, and two or more chronic conditions, and a lack of social or familiar support
Cork/Kerry (Ireland)	Older people (≥ 75 years old) with mild to moderate frailty
Rijeka (Croatia)	Patients who had a myocardial infarction, with inclusion after the clinical phase of rehabilitation
Rotterdam (the Netherlands)	Patients who had an ischemic stroke
Treviso (Italy)	Mild cognitive impairment and/or frailty, in combination with hypertension, or diabetes or cardiovascular diseases
Valencia (Spain)	Mild to moderate frailty

We aim to include 1680 *older people* (i.e. patients, clients) in total: 120 participants in the intervention group and 120 participants in the control group in each site. Study participants will be included if they: (i) are aged ≥ 65 years, (ii) have a confirmed diagnosis of the targeted chronic condition at the time of enrolment, (iii) are community-dwelling (not living in long-term care facilities) or are temporarily in a hospital or institution and are expected to be referred to their home, and (iv) are able to give informed consent.

With regard to the older people enrolled in the study, the researcher will ask the participant whether they have an informal caregiver, and will ask who is/are the most relevant formal caregivers. These informal and formal caregivers will be approached (with the permission of the participant) and invited to participate in the study. In each of the seven sites, we aim to enrol 50–70 *informal caregivers* (e.g. relatives, friends) and 30–40 *health and social care practitioners* who work with older people having the targeted condition.

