## Discussion

This study aims to evaluate the ValueCare approach in comparison with ‘usual care’ practices in terms of benefits for the target groups (older people, their informal caregivers, and health and social care practitioners), and to evaluate implementation outcomes. Benefits of the intervention will be measured in multiple domains; for older people: health-related quality of life (HR-QoL), frailty, comorbidities, loneliness, activities of daily living, falls, BMI, smoking status, alcohol consumption, physical activity, nutrition and undernutrition, medication intake, and care utilization; for informal caregivers: health-related quality of life, caregivers’ burden, and autonomy and control; for health and social practitioners: health-related quality of life, working conditions, job satisfaction, and work-related burnout. Implementation outcomes will be measured in terms of acceptability, appropriateness, feasibility, fidelity, and costs. A pre-post controlled design is used to explore the effects of the ValueCare approach in seven European sites in Athens, Greece; Coimbra, Portugal; Cork/Kerry, Ireland; Rijeka, Croatia; Rotterdam, the Netherlands; Treviso, Italy, and Valencia, Spain.

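### The caregiver and practitioner hypothesis is set as follow-up against baseline, which conflicts with the usual-care comparison described elsewhere, and the analysis section does not settle the contrast

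*Protocol article*

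**What the plan says.** All references are to the protocol article.

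- **Section on wellbeing, perceived burden and (job) satisfaction outcomes (with Table 4):** for caregivers and practitioners, "we hypothesise more favourable results at follow-up compared to baseline measurement". Table 4 labels these measures as effectiveness outcomes.
- **Discussion:** "This study aims to evaluate the ValueCare approach in comparison with ‘usual care’ practices in terms of benefits for the target groups". The parenthesis that follows names older people, informal caregivers and practitioners.
- **Study design:** a controlled pre-post design with a ValueCare group and a usual-care group, measured at baseline, 12 and 18 months.
- **Abstract, Methods:** after listing outcomes for all three groups, it says that regression will evaluate differences between intervention and control.
- **Hypotheses:** "we expect a lower caregiver burden, and improved wellbeing and (job) satisfaction among participants in the intervention group".
- **Objectives:** for older people, "To compare the benefits of the ValueCare approach versus usual care for older people"; for the other two groups, only "To evaluate the benefits of the ValueCare approach for older people’s caregivers" and practitioners, with no comparator.
- **Participants:** caregivers are reached through the enrolled older people: "These informal and formal caregivers will be approached (with the permission of the participant) and invited to participate in the study". The targets are 50–70 informal caregivers and 30–40 practitioners per site, with no division by group.
- **Data management and analyses:** multilevel regression of differences between T0, T1 and T2. Neither a group term nor a group-by-time term is named.

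**The concern.** The article gives two different contrasts for the same outcomes. One is improvement over time within respondents; the other is intervention against usual care. They answer different questions, and only the second separates the effect of ValueCare from whatever else changes over 12 to 18 months.

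What is at stake is the second objective, benefit for caregivers and practitioners. If the before-after contrast is the one analysed, that objective has no counterfactual. A general improvement would look like a benefit, and a general worsening would hide one. The main outcome, PROMIS-10 in older people, is not affected by this point.

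**Working it through.** **Reading the sections together.** The Abstract, Study design and Discussion point to a between-group comparison. The outcome section for caregivers and practitioners points to a before-after comparison. The Hypotheses sentence locates the benefit in the intervention group, which suggests a comparison but does not state one. The second objective names no comparator. The analysis section, where the matter should be settled, mentions only time points. A before-after reading is not far-fetched: the same section plans a preliminary cost-effectiveness analysis that uses the baseline measurement as control.

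**Size of the consequence.** The article gives no power calculation or effect size for these two groups, so there is no figure to reproduce. The following is an illustration.

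Inputs from the article:
- informal caregivers: 7 × 50–70 = 350–490
- practitioners: 7 × 30–40 = 210–280
- significance level 0.05 (taken as two-sided)

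Assumptions not in the article:
- half of each group is on the intervention side: n = 175–245 caregivers, 105–140 practitioners
- pre-post correlation ρ = 0.5
- no attrition and no clustering
- no effect of ValueCare, but a favourable background drift d of 0.1–0.3 SD

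Standard error of the mean paired change, in SD units: SE = √(2(1 − ρ)/n).

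- n = 175: √(1/175) = 0.0756
- n = 245: √(1/245) = 0.0639

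Probability of a significant improvement ≈ Φ(d/SE − 1.96); the opposite tail is negligible. For d = 0.2:

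- n = 175: Φ(2.646 − 1.96) = 0.75
- n = 245: Φ(3.130 − 1.96) = 0.88

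| Drift with no true effect | Caregivers, n = 175–245 | Practitioners, n = 105–140 |
|---|---|---|
| 0.1 SD | 26–35% | 18–22% |
| 0.2 SD | 75–88% | 54–66% |
| 0.3 SD | 98–100% | 87–94% |

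The nominal rate is 5%. With ρ = 0.7 the upper ends for caregivers rise to 52%, 98% and 100%. With 20% attrition, the figure the article assumes for older people, the caregiver n is 140–196, and with ρ = 0.5 the 0.2 SD row becomes 66–80%.

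**What the between-group contrast offers.** Drift common to both groups cancels. With a 1:1 split, ρ = 0.5, 80% power and baseline adjustment, the detectable difference is (1.96 + 0.84) × √(2(1 − ρ²)/n), with n per group:

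- caregivers: 2.80 × √(1.5/175) = 0.26 SD down to 2.80 × √(1.5/245) = 0.22 SD
- practitioners: 0.34 SD down to 0.29 SD

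With 14 clusters and the article's intra-class correlation of 0.02 (given there for older people), the design effect is 1 + (m − 1) × 0.02:

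- caregivers, m = 25–35: 1.48–1.68, giving about 0.32–0.28 SD
- practitioners, m = 15–20: 1.28–1.38, giving about 0.38–0.34 SD

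**The case against.** The sentence at issue sits in a section that introduces outcome measures. It states an expected direction and prescribes no test. The Abstract already promises a between-group regression, and a full protocol or analysis plan, not shown here, would normally fix the exact contrast. The t tests in the analysis section concern implementation outcomes, not these measures. All of this stands, and it makes the bias conditional: it arises only if the before-after hypothesis is the one analysed. It does not remove the conflict, because the article does not leave the contrast open. It states one, and that one disagrees with its own aim.

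A reader might go further and infer that caregivers of control participants are enrolled and their data would be discarded. The article does not say this. Participants sets no restriction to the intervention group, which makes control-side enrolment plausible. But the missing comparator in the second objective, and the outcome section's reference to people engaged in implementing ValueCare, also allow an intervention-only reading. On that reading there are no control data to discard, and restoring a comparator would take more than rewording.

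A reader might also infer that natural improvement will be credited to ValueCare. The article gives no information on how burden or job satisfaction changes without the intervention, and in the frailty and cognitive-impairment sites worsening is at least as conceivable. The size and direction of drift are therefore assumptions, and the percentages show sensitivity to drift, not a forecast.

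**Conclusion.** The inconsistency is real and in the current text. For caregivers and practitioners the article states a follow-up-versus-baseline hypothesis, describes a usual-care comparison elsewhere, and has an analysis section that does not decide between them. If the before-after contrast is followed, background change in either direction cannot be told apart from an effect of ValueCare.

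Under the assumptions listed with the calculation, with ρ = 0.5, a favourable drift of 0.1–0.3 SD and no true effect would be declared significant for caregivers in roughly 26–100% of studies; for 0.2 SD it is about 75–88%. An unfavourable drift would mask a benefit. The point should be corrected before analysis. It concerns the second objective only, and it does not show that a wrong analysis has been fixed.

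**What to change.** 1. Restate the hypothesis in the caregiver and practitioner outcome section, and the matching analysis in Data management and analyses, as the intervention-versus-control difference in change from T0 to T1 and T2. Use a multilevel model with a group-by-time term or baseline adjustment, for each of the two groups separately.
2. Report within-group change descriptively only.
3. State how the 50–70 and 30–40 per-site targets divide between intervention and control.
4. If only intervention-side caregivers and practitioners are measured, say so, label the results for the second objective as descriptive, and remove these two groups from the usual-care comparison in the Discussion, with the Abstract brought into line.

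**Cost.** Where control-side respondents are enrolled, the change is to the text and the model specification. The price is precision: with 175 per group and ρ = 0.5, the standard error goes from 0.0756 for a before-after change to √(1.5/175) = 0.0926 for a baseline-adjusted group difference, about 22% larger. Where control-side respondents are not enrolled, item 4 needs only wording, whereas a controlled comparison would need additional recruitment.

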#### Evaluation of implementation outcomes in terms of acceptability, appropriateness, feasibility, fidelity, and costs

Table 5 provides the implementation outcomes and related measures for evaluating the performance of the ValueCare approach implementation across the seven sites. The implementation outcome evaluation is based on the taxonomy of implementation outcomes defined by Proctor et al. (2011) [60]. Included implementation outcomes are acceptability, appropriateness, feasibility, fidelity, and costs [60]. A mixed methods approach is used to collect implementation outcomes. This includes the 12-month self-reported follow-up questionnaires (*T*_1_), focus group interviews and data routinely collected by the ValueCare application. Focus groups will be held with older people, informal caregivers, and health and social care practitioners 12 months after implementation, and at the end of the intervention. At least 2 focus groups will be held in each site with *n* = 8–12 participants per focus group. Participants will be asked to share their experiences, for example, regarding shared-decision making, satisfaction with care, perceived fit and barriers and facilitators to implement the ValueCare approach.

**Table 5 Tab5:** Implementation outcomes

Outcome	Outcome measure(s)	Methods and instruments	Target group(s)
Acceptability: willingness to receive the service offered	Enrolment rate (%)	Comparison of reported enrolment rates and targets set for the study	Older people
	Attrition/retention rate (%)	Descriptive statistics and reasons for non-consent	Older people
	Engagement	*T*_1_ follow-up questionnaire. Examples of items: engagement of patient in care plan, app functions used, cooperation between patient and care team members	All
	Perceived acceptability	4-item Acceptability of Intervention Measure (AIM) scale [61]	All
		Focus group interviews with a sample of patients, informal caregivers, and care team members	All
Appropriateness: perceived fit, relevance and compatibility of the service	Perceived fit	4-item Intervention Appropriateness Measure (IAM) scale [61]	All
		Focus group interviews with a sample of patients, informal caregivers, and care team members	All
Feasibility: extent to which a service is successfully used	Training of end users	Evaluation of training materials	All
	Perceived delivery of the intervention	4-item Feasibility of Intervention Measure (FIM) scale [61]	All
	Perceptions of barriers and facilitators	Focus group interviews with a sample of patients, informal caregivers, and care team members	All
Fidelity: extent to which the service was implemented as prescribed in the original protocol	Engagement rate (% at least one month app use)	Descriptive statistics	All
		Several items in the *T*_1_ follow-up questionnaire	
		Focus group interviews with a sample of patients, informal caregivers, and care team members	
	Dose delivered (completeness)	File analysis and *T*_1_ follow-up questionnaire: presence of care plan, app functions used, number of (digital) interactions between patients and care team	All
	Perceived quality of the delivery	Focus group interviews with a sample of patients, informal caregivers, and care team members	All
Costs: from a societal perspective	Productivity losses	iMTA Productivity Cost Questionnaire (iPCQ) [62]	Older people, informal caregivers
	Health care use	SMRC Health Care Utilization questionnaire [53]	Older people
	Quality of life	EQ-5D-5L [63]	Older people

The costs of implementing the ValueCare approach in each setting will be estimated and reported using standard procedures [64, 65]. The direct costs of using all types of health and social care services will be measured by a modified version of the SMRC Health Care Utilization questionnaire [53]. Services specific to the ValueCare implementation including training, outreach services, and time spent by care team members on elements of the program will be captured and quantified. Real cost prices will be used when unit resource prices are not available. The iMTA Valuation of Informal Care Questionnaire (iVICQ) is used to report an informal caregiver’s time spent on activities to care for a patient. Societal costs will be calculated by productivity losses for informal caregivers who perform paid labour during the study period using the friction cost method [66]. The incremental cost-effectiveness ratio (ICER) will be expressed as costs per quality-adjusted life years (QALYs) gained, based on EQ-5D-5L scores

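### Enrolment against a recruitment target does not show willingness to receive ValueCare, and reasons given by people who refused consent cannot explain attrition

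*Protocol article*

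**What the plan says.** In the protocol article, the section on implementation outcomes presents Table 5 as the means of "evaluating the performance of the ValueCare approach implementation across the seven sites". The construct is given as "Acceptability: willingness to receive the service offered", with four measures beneath it:

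- **Enrolment rate (%)**, for older people, by "Comparison of reported enrolment rates and targets set for the study".
- **Attrition/retention rate (%)**, for older people, by "Descriptive statistics and reasons for non-consent".
- **Engagement**, for all target groups, from the 12-month questionnaire, with items such as "engagement of patient in care plan, app functions used, cooperation between patient and care team members".
- **Perceived acceptability**, for all target groups, by the four-item AIM scale and focus groups.

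The target for older people is in the Participants section: "120 participants in the intervention group and 120 participants in the control group in each site", 1680 in total. Under Study design, the control group receives usual care. Under Recruitment, a person counts as enrolled after consenting and taking part in the baseline data collection; the definition does not differ by group. The Power calculation assumes 20% loss by 12 months and gives disability, moves, death and withdrawal as examples of causes.

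**The concern.** A measure of willingness needs the people who were offered the service in its denominator. A recruitment target is a number fixed by the sample size, and it is reached or missed for reasons that include how many people were approached and for how long. Setting enrolment against it answers a different question from the one that the definition asks.

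The attrition row has a separate fault. Its reason category describes people who declined at the outset, whereas attrition concerns people who consented and later left.

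Acceptability is named in the third study objective. The other two measures, the questionnaire items with the AIM scale and the focus groups, are collected around 12 months or at the end of the intervention, so they reach mainly people who accepted and stayed. Those who declined or left are seen chiefly through the enrolment and attrition rows. If those rows do not carry the information, the study will say little about unwillingness, which is the part of acceptability that matters most for wider adoption.

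**Working it through.** **Step 1. The plan's own figures.** Inputs: 7 sites, 120 + 120 per site (Participants), 20% loss (Power calculation).

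- Enrolment target: 7 × 240 = 1680, as stated.
- Per group: 7 × 120 = 840, so controls are 840/1680 = 50% of the target.
- Expected completers: 840 × 0.8 = 672 per group and 1680 × 0.8 = 1344 in total, as stated.

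These are all the quantities in the article against which enrolment and attrition of older people could be set. All targets are counts; no target consent proportion is given.

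**Step 2. Enrolment against target, intervention group only.** This is the reading most favourable to the plan. The measure is enrolled/target. The numbers invited are assumed, because the article gives none.

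| Invited (assumed) | Enrolled | Enrolled/target | Enrolled/invited |
|---|---|---|---|
| 130 | 120 | 120/120 = 100% | 120/130 = 92.3% |
| 400 | 120 | 120/120 = 100% | 120/400 = 30% |

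The measure in Table 5 is the same in both rows, although willingness differs about threefold (92.3/30 = 3.1). Restricting the row to the intervention group does not cure this.

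**Step 3. The attrition row.** Under the Recruitment section, everyone enrolled has consented. Attrition is counted among the enrolled. The set of people with reasons for refusing consent and the set of people who can drop out do not overlap, so the first cannot explain the second. The row does not list reasons for withdrawal. The protocol expects some loss from disability, moves and death, so a crude rate mixes these with unwillingness.

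**Step 4. What follows if the arm is left unnamed.** With 1:1 enrolment, a pooled rate is the mean of the two group rates. With assumed attrition:

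| Intervention | Control | Pooled |
|---|---|---|
| 30% | 10% | (30 + 10)/2 = 20% |
| 10% | 30% | (10 + 30)/2 = 20% |
| 20% | 20% | (20 + 20)/2 = 20% |

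All three equal the planning figure of 20%, so a pooled rate could not tell them apart. The article does not say that the rates will be pooled; this shows only why the arm should be named. The Data management and analyses section does not settle it, since it describes the quantitative analysis of implementation outcomes as change from baseline to follow-up and not as a comparison of groups.

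**The case against.** The strongest case on the other side has five parts.

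- **Arms.** A reader might infer that both rates are taken over intervention and control participants together, so that half the figure comes from people never offered the service. The document does not say so. The target-group column separates older people, caregivers and practitioners, not arms. Rows marked for all groups include app use, which can concern only ValueCare users, and the table is about implementing ValueCare. Targets and expected completers are also given by arm. This stands: the arm is unstated, and pooling is not planned in the text.
- **Other measures.** A reader might infer that acceptability rests on these two rates alone. It does not: engagement, the AIM scale and focus groups address ValueCare directly. Nor does any rule turn one rate into a finding of full acceptability. This also stands and limits the point to two of four measures.
- **Denominator.** The table speaks of an enrolment rate in percent without defining it, so consented over approached is compatible with the label. This stands only in part. The stated comparator is the study target, and the targets are counts. A consent proportion would have no target in the article to be compared with.
- **Condensed article.** Denominators and attrition by arm may be set out in a fuller document. That is a fair answer to anything merely absent. It does not answer a comparator that is stated and does not fit its definition, or a reason category placed under the wrong rate.
- **Attrition still informs.** To say that attrition does not measure acceptability would go too far. Intervention-group attrition carries some information, and control attrition is a useful reference if the groups are shown separately.

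**Conclusion.** The point holds in a limited form. As stated, the enrolment measure gives recruitment performance and not the share of people offered ValueCare who accepted it, whichever arm it covers. The reason category in the attrition row belongs to people who never enrolled. Neither row names the arm.

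The size cannot be computed, because the article reports no invitation, consent or attrition rates by arm. The 92% against 30% contrast and the 30%/10% attrition split are illustrations with assumed inputs; the 840 of 1680 comes from the document. The conclusion assumes that the study targets in Table 5 are the recruitment counts in the Participants section, which are the only enrolment targets given there for older people in the evaluation.

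The consequence is confined to two of four descriptive implementation measures. The PROMIS-10 main outcome, the sample size and the effectiveness comparisons are unaffected. This is a cheap improvement worth making.

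**What to change.** Change the two rows of Table 5 as follows.

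1. **Enrolment, for acceptability:** people who consented divided by people eligible and invited, in the intervention settings. Give the same ratio in the control settings as a reference for the burden of taking part in the study.
2. **Enrolment against target:** keep it, but report it separately and label it recruitment performance.
3. **Attrition:** report by group, with reasons for withdrawal, keeping death, disability and moves apart from unwillingness to continue.
4. **Reasons for refusing consent:** move to the enrolment row.

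Cost: a few lines in the table and a log of invitations by setting. Intervention and control settings are chosen in advance, so the count can be kept by arm, but it has to be made during recruitment because it may not be recoverable later. Where no log exists, the row should be relabelled as recruitment performance and the gap stated.

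Two limits remain. People who come forward after seeing posters or brochures have no invitation denominator and must be reported apart. Consent also still mixes willingness to join the research with willingness to receive the service; the control-setting ratio helps to interpret this but does not remove it.
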